### Inclusion and exclusion criteria

Any student enrolled in this particular university who is 18 years or older is eligible to attend the study. Serious and severe mental illness and high risk of self-harm/harm to others would be exclusion criteria as these individuals may require a more individual and tailored support and would be unlikely to benefit from a standalone group intervention. Scoring below the threshold of Beck Anxiety Inventory (BAI) for CBT study and Difficulties in Emotion Regulation Scale (DERS) for DBT study constitutes another exclusion criteria.

### Procedure

The language of the interventions, questionnaires, and the interviews are in Turkish. University’s psychological counseling centre is a stakeholder. An email invitation addressing the students and asking them to attend anxiety management or emotion regulation groups will be sent via the university’s psychological counseling centre. The volunteers who meet the clinical threshold for their respective groups will be invited to the groups on a first come first serve basis and receive either a group CBT intervention for anxiety-management or a group DBT-informed psychotherapy intervention for emotion regulation, based on their preference. If there are any volunteers who cannot be invited to the initial groups due to capacity, they will be placed on a waitlist and will be informed of this. All individuals who applied to join the groups will have eventual access to the intervention.

The interventions will last eight sessions and will be held on-site at campus in the university’s psychological counseling centre’s group rooms. The participants will not be allowed to attend the anxiety management and emotion regulation groups at the same time. The therapy groups will be facilitated by trainee or qualified clinical psychologists and/or trainee or qualified psychological counselors supervised by the first author. Data collection will be conducted online and in-session. For in-session quantitative data collection, separate research assistants will be employed. Further information on data-collection is provided below under “Data collection” section.

Participants will be asked to complete a batch of questionnaires at baseline, during and after the intervention, and after approximately 6 weeks follow-up. Furthermore, following the completion of the groups, qualitative data will be collected to explore the participants’ experiences and views on the group intervention they received. Although the study does not include an active control group, the waitlist controls will provide a reference condition that allows for comparison with the intervention group and enable a more accurate evaluation of the results. Tables 1 and 2 present full schedules of the assessment plans.

**Table 1 ibag010-T1:** Assessment Plan for the CBT group.

	Baseline assessment (t0)	Weekly assessment	Post-intervention assessment (t1)	Follow-up assessment (t2)
Socio-demographic Form	X			
Depression Anxiety and Stress Scale (DASS-42)	X		X	X
Beck Anxiety Inventory (BAI)	X		X	X
Generalized Anxiety Disorder-7 (GAD-7)	X		X	X
Patient Health Questionnaire-9 (PHQ-9)	X		X	X
Outcome Rating Scale (ORS)		X		
Group Session Rating Scale (GSRS)		X		
Client Feedback Form			X	

*Note.* ORS will be completed at the beginning of each session. GSRS will be completed at the end of each session.

**Table 2 ibag010-T2:** Assessment plan for the DBT-informed group.

	Baseline assessment (t0)	Weekly assessment	Post-intervention assessment (t1)	Follow-up assessment (t2)
Socio-demographic Form	X			
Borderline Evaluation of Severity Over Time (BEST)	X		X	X
Difficulties in Emotion Regulation Scale (DERS)	X		X	X
Depression Anxiety and Stress Scale (DASS-42)	X		X	X
Generalized Anxiety Disorder-7 (GAD-7)	X		X	X
Patient Health Questionnaire-9 (PHQ-9)	X		X	X
Outcome Rating Scale (ORS)		X		
Group Session Rating Scale (GSRS)		X		
Client Feedback Form			X	

*Note.* ORS will be completed at the beginning of each session. GSRS will be completed at the end of each session.

### Data collection

As this is a mixed-methods study, standardized measures and qualitative interviews will be used for data collection.

The measures used in this project are self-report instruments. Digitally completed baseline questionnaires will be filled out independently by the participants through Qualtrics [41].

Questionnaires administered at the beginning and the end of each session after the completion of the intervention will be filled out on paper and will be administered by research assistants, who will be either undergraduate or postgraduate students in psychology or psychological counseling programs. The research assistants will receive a training session led by the first author on procedures, ethics, and supporting participants, as well as ongoing supervision.

All measures, except for ORS and GSRS, will initially be administered online, so no additional data collection framework is required. Information on qualitative interviews is detailed under “Qualitative interviews” section, and data protection is discussed under “Data protection, confidentiality, and safety” section.

The questionnaires for assessment are specifically selected, considering their high validity and reliability which have been demonstrated in studies conducted with university samples. For anxiety management groups, Depression Anxiety and Stress Scale (DASS-42; adapted to Turkish by Bilgel & Bayram [42]), Beck Anxiety Inventory (BAI; adapted to Turkish by Ulusoy *et al.* [43]), Generalized Anxiety Disorder-7 (GAD7; adapted by Konkan *et al.* [44]), Patient Health Questionnaire (PHQ9; adapted by Sari *et al.* [45]) will be asked to be completed once before and once after the intervention, and approximately 6 weeks after the completion of the intervention (follow-up).

For emotion regulation group, Borderline Evaluation of Severity Over Times (BEST; adapted to Turkish by Akın [46]), Difficulties in Emotion Regulation Scale (DERS; adapted to Turkish by Rugancı and Gençöz [47]); Depression Anxiety and Stress Scale (DASS-42; adapted to Turkish by Bilgel and Bayram [42]), Generalized Anxiety Disorder-7 (GAD7; adapted by Konkan *et al.* [44]), Patient Health Questionnaire (PHQ9; adapted by Sari *et al.* [45]) will be asked to be completed once before and once after the intervention, and approximately 6 weeks after the completion of the intervention (follow-up).

For both groups, the Outcome Rating Scale (ORS; created by Miller *et al.* [48] and translated by the project team with the permission of the creator) will be asked to be completed at the beginning of each session while Group Session Rating Scale (GSRS; created by Quirk *et al.* [49] and translated by the project team with the permission of the creator) will be asked to be completed at the end of each session. Additionally, a socio-demographic form will be asked to be completed before the intervention, and a participant feedback form put together by the project team at the end of the intervention.

#### Depression anxiety and stress scale

DASS-42 was developed by Lovibond and Lovibond [50] to measure depression, anxiety and stress and was adapted to Turkish by Bilgel and Bayram [42]. The 42-item scale demonstrated good validity and reliability for university students.

#### Beck anxiety inventory

BAI is a 21-item tool that is developed to measure the severity of anxiety [51]. The Turkish adaptation of BAI has good psychometric properties [43]. It is a valid and reliable measurement tool to assess anxiety in a university sample.

#### Generalized anxiety disorder-7

GAD-7 is a brief questionnaire developed by Spitzer *et al.* [52] to assess generalized anxiety symptoms. The Turkish adaptation of GAD-7 demonstrated high validity and reliability [44].

#### Patient health questionnaire-9

PHQ-9 is a widely used tool to measure the severity of depressive symptoms. The 9-item self-report measure was developed by Kroenke *et al.* [53] and adapted to Turkish by Sari *et al.* [45]. The Turkish PHQ-9 has been found reliable, making it suitable for evaluation of depression.

#### Borderline evaluation of severity over time

BEST is a self-report measure, designed by Pfohl *et al.* [54] to assess the severity of borderline personality disorder symptoms over time. The adaptation of the measure was carried out by Akın [46], it demonstrated high validity and reliability.

#### Difficulties in emotion regulation scale

DERS is a 36-item measure developed by Gratz & Roemer [55] to assess emotion regulation difficulties. It was adapted to Turkish by Rugancı & Gençöz [47], demonstrating good psychometric properties.

#### Outcome rating scale

The ORS was developed by Miller *et al.* [48] as a brief assessment tool to measure therapeutic progress. The scale is translated by the project team with the permission of the creator.

#### Group session rating scale

The GSRS was developed by Quirk *et al.* [49] to measure the group therapy process from the participants’ perspectives. The scale is translated by the project team with the permission of the creator.

#### Socio-demographic form

The socio-demographic form is prepared by the project team. The self-report questionnaire is used to gather information about the demographic characteristics of the participants including age, gender and income level. Data about the academic background of the participants including major, GPA, and academic success will also be obtained through the questionnaire.

#### Client feedback form

The client feedback form is a 4 point Likert scale with 10 items and a free text box for comments, developed by the first author who was inspired from a feedback form used at University of Essex Doctorate in Clinical Psychology Programme. It is used to gather information about the participants’ experience with the group facilitator and the intervention. The participants will give feedback about their satisfaction level with the service they received, and the answers will be collected anonymously. The form includes questions about the therapeutic process, the structure of the sessions, the therapist’s approach, and whether the support was helpful.

#### Qualitative interviews

Participants who attend the groups, including those who dropped out, will be invited to attend an interview for in-depth qualitative feedback after the intervention, including reasons for dropout if appropriate. Qualitative data will be collected from 6 to 20 participants from anxiety management and 6 to 20 participants from emotion regulation groups, where they will be invited to share their experiences and thoughts about the difficulties and the group they attended. Participation in the interviews is entirely voluntary, and potential participants are not to be rejected from the studies if they do not wish to attend an interview. The interviews will be recorded using either a voice recording device or a password protected computer with the written permission of the participants. The interviews will be transcribed manually by the trainees who conducted them. The sample questions to be asked to the participants are: (i) Could you tell us a little about the process (your mental health difficulties) that led you to apply to this group? (ii) Were you satisfied with the group? (iii) Which parts of the group were useful to you? (iv) Which parts of the group need to change (what you didn’t like)? (v) How was your relationship with the therapist and assistants? (vi) How was your relationship with the other participants of the group? (vii) What was the most important thing you learned from the group? (viii) Are there any other things that stood out to you? (ix) Would you recommend this group to other students with similar problems? (x) Do you think this group should be an ongoing service provided by the university?

## Data analysis

### Investigating the feasibility and acceptability of recruitment and delivery

To evaluate the acceptability and feasibility of these conducted groups, completion rates, number of attended sessions, drop-out rates, perceived burden and inconvenience of attending groups, and reasons for non-completion, the client feedback form and in-depth qualitative interviews will be investigated and/or analyzed.

### Investigating effectiveness

Quantitative data on anxiety, depression, stress, emotion regulation difficulties, borderline symptoms, and general wellbeing collected via questionnaires in Tables 1 and 2 will be analyzed using descriptive and inferential statistics, and clinically significant change analysis [56] to see whether there was meaningful change in participants’ psychological difficulties and wellbeing following the completion of the group intervention. Reflexive Thematic Analysis conducted using qualitative data will also inform the effectiveness.

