**Results:**

Standardized measures of anxiety or emotion regulation are administered at baseline, post-intervention, and six-week follow-up for both experimental and waitlist arms. Qualitative data are collected through semi-structured interviews conducted after intervention completion.

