#### Third stage—implementation of culturally adapted interventions

The effectiveness and feasibility of both interventions will be investigated. This stage adopts a mixed-methods non-randomized pre-post design with a waitlist control and approximately 6 weeks follow-up. These feasibility studies are registered on clinicaltrials.gov with the identification numbers NCT07096154 and NCT07096141 for group CBT and group DBT interventions respectively.

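### Effectiveness is worded as change after the group in students selected for high scores on the outcome scale and is not tied to the waitlist, so regression to the mean can be read as benefit

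*Protocol article*

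**What the plan says.** **Entry.** Under Inclusion and exclusion criteria, "Scoring below the threshold of Beck Anxiety Inventory (BAI) for CBT study and Difficulties in Emotion Regulation Scale (DERS) for DBT study" is a ground for exclusion. The threshold values are not given.

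**Outcome.** Under Data collection, the questionnaires, BAI and DERS among them, "will be asked to be completed once before and once after the intervention, and approximately 6 weeks after the completion of the intervention (follow-up"). Tables 1 and 2, which the Procedure section presents as full schedules, list no screening score separate from t0.

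**Effectiveness.** Under Investigating effectiveness, the questionnaire data go to descriptive and inferential statistics and to "clinically significant change analysis [56] to see whether there was meaningful change in" the students' difficulties and wellbeing once the group is over. No comparison between arms is named there.

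**Waitlist.** The third stage is a "mixed-methods non-randomized pre-post design with a waitlist control and approximately 6 weeks follow-up". The Procedure section says that "the waitlist controls will provide a reference condition that allows for comparison with the intervention group", and the abstract says that the measures are "administered at baseline, post-intervention, and six-week follow-up for both experimental and waitlist arms". The waitlist consists of volunteers who exceed the capacity of the initial groups, if there are any. Places go in order of response.

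**The concern.** A score that had to be high for a student to enter is, on average, lower when taken again, even if nothing has been done. When that same score is the starting point for change, the fall is counted as improvement. The effectiveness section poses its question as change after the group, and a reader who follows that wording has no instruction to subtract what happened on the waitlist.

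The article aims to assess effectiveness, hopes to promote the programmes to other counselling centres, and intends to inform a later randomized trial. An effect size taken from uncontrolled change would mislead on all three. The Limitations section mentions the missing active control but not selection on the outcome scale.

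**Working it through.** The plan has no figure of its own to reproduce here: it gives no effect size, SD, retest correlation, alpha or power.

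**Inputs from the article.** Selection on BAI or DERS; the same scale at t0, t1 and t2; up to 60 participants per study across both arms.

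**Assumptions.** Normally distributed scores in applicant SD units; no treatment effect; retest correlation r of 0.6 to 0.8; threshold z from -0.5 to +1 SD relative to the applicant mean; an equal split, so 60/2 = 30 treated students; selection on the t0 score.

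**Formulas.** With λ = φ(z)/(1 - Φ(z)):

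- expected fall = (1 - r)λ
- variance of entry scores after selection: V = 1 - λ(λ - z)
- SD of change = √[(1 - r)²V + 1 - r²]

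**Three cases worked through.**

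- z = -0.5, r = 0.8: λ = 0.509, fall = 0.2 × 0.509 = 0.10; V = 1 - 0.509 × 1.009 = 0.486; SD of change = √(0.04 × 0.486 + 0.36) = 0.616; ratio 0.165; times √30 = 0.90.
- z = 0.5, r = 0.7: λ = 1.141, fall = 0.3 × 1.141 = 0.34; V = 1 - 1.141 × 0.641 = 0.269; SD of change = √(0.09 × 0.269 + 0.51) = 0.731; ratio 0.468; times √30 = 2.56.
- z = 1, r = 0.6: λ = 1.525, fall = 0.4 × 1.525 = 0.61; V = 1 - 1.525 × 0.525 = 0.199; SD of change = √(0.16 × 0.199 + 0.64) = 0.820; ratio 0.744; times √30 = 4.08.

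Simulation gives a significant two-sided paired t-test (5% level, n = 30) in about 14%, 70% and 98% of trials in these cases, against a nominal 5%.

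**Full range.** Each cell runs from r = 0.8 to r = 0.6. The last two columns count students who fall below the entry threshold and also change by more than 1.96 × √2 × √(1 - reliability) in applicant SD units. They use either r or 0.9 as the reliability.

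| Threshold z | Fall (SD) | Paired test significant | Below threshold at retest | False responders, reliability = r | False responders, reliability = 0.9 |
|---|---|---|---|---|---|
| -0.5 | 0.10-0.20 | 14-25% | 13-19% | 2-3% | 5-11% |
| 0 | 0.16-0.32 | 28-53% | 20-30% | 3-4% | 8-18% |
| 0.5 | 0.23-0.46 | 51-83% | 29-42% | 4-6% | 11-25% |
| 1 | 0.31-0.61 | 76-98% | 38-54% | 6-8% | 15-34% |

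**With the waitlist.** If both arms pass the same threshold, are measured at the same times and are otherwise comparable, the expected difference is (1 - r)λ - (1 - r)λ = 0. In simulation with 30 against 30, the test of the between-arm difference in change rejects in about 5% of trials.

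**The case against.** The strongest reply is that the article does provide a control. The waitlist is part of the stated design, is measured at the same three times, and is there for comparison. The phrase on inferential statistics does not exclude a between-arm test, and the model, covariates and intervals may sit in a plan that is not shown. This stands against two stronger readings. A reader might infer that only treated students will be analysed, or that regression to the mean will certainly be reported as benefit. The documents support neither: the effectiveness section does not restrict the analysis to the treated arm.

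A reader might also take the 13 to 54% who fall below the entry threshold as the rate of false clinically significant change. That is not supported either. The article defines the method only by a citation. If the method also requires reliable change, the rate is about 2 to 8% or 5 to 34%, depending on the reliability used. Mean change is the more exposed measure.

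Finally, one might infer that contrasting the arms disposes of the artefact completely. It does not: arms form by order of response, and a waitlist exists only if demand exceeds capacity, so the arms may differ or the control may be small.

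What survives is narrower. The article does state which question decides effectiveness, words it as change after the group, and leaves the waitlist out. That is a stated criterion that can be improved, rather than an omitted detail.

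**Conclusion.** The point holds in conditional form: regression to the mean can appear as benefit if within-group change is read as effectiveness, and the current wording permits that reading. Under no treatment effect, the expected fall is about 0.10 to 0.61 SD and a paired test at n = 30 is significant in about 14 to 98% of trials.

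The width of these ranges reflects unknown inputs. The threshold, the retest correlation and the number treated are all assumed, and selection is taken to act on the t0 score because no other screening score is listed. The low end belongs to a lenient threshold and a stable scale, and even there the error rate is well above 5%. The figures describe the uncontrolled reading only.

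**What to change.** In Investigating effectiveness, state that:

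- the effectiveness estimate is the group-minus-waitlist difference at t1 in BAI (CBT study) or DERS (DBT study), adjusted for the t0 score on the same scale (ANCOVA), with a 95% confidence interval;
- clinically significant change is reported in both arms;
- within-arm change is descriptive and not evidence of effectiveness, including when too few students are waitlisted for a useful comparison;
- allocation follows order of response, so the contrast removes regression to the mean only as far as the arms are otherwise comparable. Baseline adjustment helps but does not guarantee this.

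**Cost.** The wording of the analysis changes; by the abstract's account both arms are already measured, so no new data are needed. The reported effect will be smaller than the raw pre-post change, because the waitlist's own fall is subtracted. It will also be less precise: with 30 per arm, the standard error of a difference in mean change is √2 = 1.41 times that of one arm's mean change. Baseline adjustment recovers only a little of this (for r = 0.7, the residual SD is √(1 - 0.49) = 0.714, against 0.731 for change at z = 0.5).

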## Ethics and data protection

Ethical clearance has been obtained from Bogazici University Institutional Review Board in Social Sciences and Humanities (SBINAREK) with the date 28/06/2024 and the number 2024-38. Amendments were then accepted on 17/01/2025. During the consent process, participants will be informed about the purpose of the study, the institutions supporting the study, and the structure of the UniWELL project. Additionally, participants will be informed about the duration and content of the group intervention and that they will be required to complete several questionnaires at separate times before, during, and after the intervention. Participants will also be informed that attending the group is entirely voluntary, that they will not receive compensation, and that choosing not to participate will not affect any services they receive from the university. Information will be provided about confidentiality procedures, how data will be stored securely, how personal information will be removed and anonymized, and how the anonymized data may later be used in scientific publications or further research. The consent process will also explain potential risks, such as the possibility of emotional discomfort when answering questionnaires, and outline the support options and crisis procedures available if needed. Finally, participants will be given the research team’s contact information and the address of the university ethics board so they can ask questions or seek clarification before deciding whether to participate. Additionally, for ethical reasons, every eligible participant, including the ones on the waitlist, will be offered a group intervention that will target their problems.

### Data protection, confidentiality, and safety

Quantitative data that are collected online will be fully anonymized after the follow up step and will be kept as an excel file on a password protected secure drive. Only the researchers who do not hold an academic position at the university will have access to identifiable information.

Quantitative data collected by using pen and paper will be locked securely in a locked cabinet in the university’s psychological counseling centre or in a campus-based office. The paper-based data will be destroyed after the information is entered on excel securely. Qualitative interview recordings will be kept securely on a password-protected device until transcriptions of the records made. Following that, the voice recordings will be permanently deleted, and the transcriptions will be stored securely on a password-protected drive. The anonymized quantitative data will be kept securely on a password protected drive for 10 years and will be shared with peer-reviewers if requested, while the qualitative interview transcripts will also be kept securely on a password protected drive but they will not be shared with peer-reviewers (will be only open to the research team) until it is deleted after 10 years. These data may be used in secondary analysis projects by some of the research team.

Participant name or any identifiable information including contact information will not to be shared in any publication or any other form of presentation. Additionally, the first author, will never have access to the names of the students who attended the study to manage their dual role as a researcher and instructor at the same university. The only exception is a high-risk situation, where a participant develops high suicidality and self-harm behaviors, and the trainee psychologists or counselors would not be able to handle the situation. If that is the case, information of the participant may be shared with people or organizations that would ensure the participant’s safety. This could include facilitating access to a psychiatric clinic or hospital. The participants will also be asked to provide an emergency contact number to ensure the participant’s safety and wellbeing in case of an emergency. This exception is included in the consent form.

